## Introduction

### Background

As a society, we are becoming more sedentary. In some countries, inactivity levels can be as high as 70%, with 1 in 4 adults and 3 in 4 adolescents not achieving the recommended World Health Organization (WHO) activity levels [1]. Recommendations for adults are as follows: “at least 150 minutes of moderate-intensity aerobic physical activity throughout the week or do at least 75 minutes of vigorous-intensity aerobic physical activity throughout the week or an equivalent combination of moderate- and vigorous-intensity activity” [2]. In a press release issued to celebrate world health data on April 7, 2020, the WHO stated that approximately 2 million deaths per year are due to low physical activity. From a global perspective, sedentary behavior is one of the 10 leading causes of mortality and morbidity [1]. Physical inactivity can significantly affect an individual’s health and quality of life and increase the probability of developing several chronic diseases such as heart disease, obesity, high blood cholesterol, and type 2 diabetes.

Every year, a large section of the global population makes resolutions that are focused on improved fitness. Unfortunately, these resolutions are not sustained, with both popular media and peer-reviewed journals reporting on the low number that maintain behavioral changes. Popular media report dramatic figures, including an analysis by Strava of their global membership data, revealing that January 17, 2020, was *quitters day*, the day individuals are most likely to give up their New Year’s resolutions [3]. Similar statistics have been reported for gym membership and use. A review by Sperandei et al [4] of over 5240 gym members revealed a dropout rate of 47% by the second month, 86% by the sixth month, and 96% by the 12th month. These figures were reinforced by a Spanish study of 14,522 gym members, which revealed that between 47.3% and 56% dropped out over the course of a year [5].

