#### Fitbit

The use of fitness trackers in this study will facilitate the objective assessment of the participants’ activity patterns and behavioral changes in exercise. It will also enable the identification of individuals who already have a well-established exercise regime. A BYOD approach will be used, and data from each participant’s Fitbit will be captured. Fitbit devices are a range of physical activity trackers and smartwatches that combine integrated accelerometers and photoplethysmograph sensors to measure motion and heart rate. Proprietary algorithms convert the accelerometer data into sleep and activity patterns. Fitbit devices use Bluetooth low energy technology to synchronize with the individual’s mobile device and produce various metrics, including step count, floors climbed, distance covered, calories burned, active minutes, sleep time and stages, and heart rate. In this study, a high-frequency intraday data will be collected using a web-based application programming interface. These data are highly granular and include 1 minute and 15 minutes for activity and 1 second and 1 minute for heart rate.

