#### Status of Change

To ensure that all participants were able to assess their current activity levels against the same criteria, the WHO physical activity guidance [27] was included in the instructions for the *stages of change* questionnaire. Participants were asked to consider only planned physical activities aimed at improving or maintaining physical fitness and health. Active periods should consist of 150 minutes of moderate-intensity physical activity (such as a brisk walk) in a week or 75 minutes of vigorous-intensity physical activity (such as a jog or run) over the course of a week. Participants will be asked to complete the status of changes questionnaire at the start of the study and 6 months after study commencement (Multimedia Appendix 3 includes details of the stages of change questionnaire and screenshots of the app).

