Finally, the question arises of how to quantify the target variable, that is, the adherence behavior, given that various types of objective fitness data will be collected. We will mainly rely on the data set of activity patterns and the step counts. According to the WHO physical activity guidelines, to improve or maintain physical fitness and health, active periods should consist of 150 minutes of moderate-intensity brisk walking or 75 minutes of vigorous-intensity jogging or running over the course of a week. If the participant completes this minimum exercise in a particular week, their adherence score for this week will be 1; otherwise, the score is 0. The scores for all weeks will be summed to obtain a total score to represent the overall adherence level of this participant.

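### The weekly adherence rule restates the WHO minimum as brisk walking, jogging or running and drops the mixed-intensity option, so some weeks that meet the guideline the article quotes would score 0

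*Protocol article*

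**What the plan says.** The article describes the weekly activity minimum in three places.

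- **Background** quotes the WHO recommendation for adults: "at least 150 minutes of moderate-intensity aerobic physical activity throughout the week", or 75 minutes of vigorous aerobic activity, "or an equivalent combination of moderate- and vigorous-intensity activity".
- **Status of Change** gives participants the same two thresholds, each with an example. The moderate one reads "150 minutes of moderate-intensity physical activity (such as a brisk walk) in a week". The vigorous one has the same form, with jogging or running as its example. It does not mention a combination.
- **Data Analysis and Computational Modeling**, where the target variable is quantified, cites the WHO guidelines and says "active periods should consist of 150 minutes of moderate-intensity brisk walking or 75 minutes of vigorous-intensity jogging or running" in a week. It continues: "If the participant completes this minimum exercise in a particular week, their adherence score for this week will be 1". Any other week scores 0, and the weekly scores are summed.

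On the data behind the score, the same section says: "We will mainly rely on the data set of activity patterns and the step counts". The Fitbit section lists active minutes and heart rate among the device's outputs, with heart rate captured at "1 second and 1 minute for heart rate". Under Research Participants, entry is open to healthy adults starting a physical activity regime, with no restriction on its type.

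**The concern.** The scoring rule claims the same authority as the other two sections but is narrower in two ways. Walking, jogging and running have changed from examples into the definition, and the option of combining intensities has gone.

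This matters because the weekly score is the target of every prediction model in the article. The study wants to identify people who give up. If a week of sustained exercise scores 0 because of its type, or because it mixes intensities, that week is indistinguishable from one with no exercise. The target then carries some information about how a person exercises as well as whether they stopped, and a predictor related to type of exercise could appear to predict abandonment. None of the candidate regression methods can correct a mislabelled target.

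**Working it through.** The plan states no figure to reproduce. The check compares the definitions and applies them to illustrative weeks.

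**Inputs**
- Moderate threshold: 150 minutes a week (all three sections).
- Vigorous threshold: 75 minutes a week (all three sections).
- Exchange rate between intensities: 150 / 75 = 2, so one vigorous minute counts as two moderate minutes. This is implied by the two thresholds; the article does not state it.
- The minutes in each example week are assumptions chosen for illustration.

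**Definitions side by side**

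| | Background | Status of Change | Scoring rule |
|---|---|---|---|
| Activity that counts | any aerobic | any, with examples | walking, jogging, running |
| Combination of intensities | yes | not mentioned | not mentioned |

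**Week A: 200 minutes of moderate cycling, no walking or running**
- Background: 200 ≥ 150, met.
- Status of Change: 200 ≥ 150, met.
- Scoring rule, read literally: 0 minutes of brisk walking and 0 of jogging or running. Score 0.

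**Week B: 100 moderate plus 40 vigorous minutes**
- Background: 100 + 2 × 40 = 180 moderate-equivalent minutes; 180 ≥ 150, met through the combination clause.
- Scoring rule: 100 < 150 and 40 < 75. Score 0. Counting the vigorous minutes one for one as moderate does not help: 100 + 40 = 140 < 150.

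Week B scores 0 even if all of it is brisk walking and jogging. The lost combination clause therefore matters even for walkers and runners, and whichever sensor supplies the minutes.

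**Effect on the total.** Each such week lowers the total by 1. Data are captured over 12 months, about 52 weeks, so the total runs from 0 to about 52. How many weeks and participants are affected depends on the types and mixes of exercise in the sample, which the article does not give.

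**The case against.** The strongest reply is that the scoring sentence is shorthand. It cites the WHO guidelines, reuses the thresholds and activities of the Status of Change section, and never says that other activity is excluded. The Status of Change section in the Introduction also says that the WHO recommendations were chosen as the study's guideline. In a condensed article this may be a loose paraphrase. That is a fair reading of intent, but the sentence is followed directly by a pass/fail rule that refers back to it, so an analyst who follows the text would apply the narrow version. It also does not bring back the combination clause, which the Status of Change wording lacks too.

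A reader might infer more than the article supports:

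- **That the score rests on step counts, so cyclists and swimmers necessarily fail every week.** The article names activity patterns before step counts and says it relies on them mainly. The device also supplies active minutes and heart rate, which could credit exercise without steps. How the minutes are derived is not described.
- **That a known number of participants would score 0 of about 52.** This needs a share of non-walking exercisers, which the article does not give, so any headcount out of 200 would only return the share assumed. It also needs those people to receive no credit in any week of the year.
- **That status of change and the target judge the same week differently.** The questionnaire is completed at the start and at 6 months and does not score weeks. The two wordings differ, but there is no week-by-week conflict.
- **That a particular trait, such as social inhibition, would become a false predictor.** Nothing in the article links it to type of exercise.

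**Conclusion.** The point holds as an inconsistency in the definition of the target variable. The scoring rule misstates the WHO minimum that the article itself quotes: examples have become requirements and the combination clause is missing. Applied as written, it scores 0 in some weeks that meet the quoted guideline, with a loss of one point per affected week. Misclassification follows from the literal wording and is not an established result of the implementation. Its overall size cannot be computed from the article. The conclusion assumes that the rule is applied as written and, for the type-of-exercise part only, that some participants do aerobic activity other than walking or running, which the entry criteria allow. Because the rule feeds every model and is cheap to correct, it should be settled before analysis.

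**What to change.** In Data Analysis and Computational Modeling, define a week as adherent if it contains any of the following:

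- 150 minutes or more of aerobic activity at moderate intensity;
- 75 minutes or more of aerobic activity at vigorous intensity;
- a mix that reaches 150 when each vigorous minute is counted as two.

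Give walking and jogging or running as examples only. Name the device variable that supplies the minutes: the intensity-based active minutes that the Fitbit already provides, rather than step counts alone. Heart rate can be an optional supplement or a sensitivity analysis. For consistency, the Status of Change wording could mention the combination as well.

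**Cost.** A rewording and some extra processing of data already being collected. Recruitment was pending when the article was submitted. The downside is that device-derived active minutes vary across the Fitbit models that participants own, so this variation should be acknowledged when the target is reported.

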**Objective:**

The aim of this study is to determine whether it is possible to use decision-making tasks such as the Iowa Gambling Task to help determine those most likely to abandon their fitness goals. Predictive models built using methods from computational models of decision-making, combining objective data from a fitness tracker with personality traits and modeling from decision-making games delivered via a mobile app, will be used to ascertain whether a predictive algorithm can identify digital personae most likely to be nonadherent to self-determined exercise goals. If it is possible to phenotype these individuals, it may be possible to tailor initiatives to support these individuals to continue exercising.

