### Study Hypothesis

The hypothesis of this study is as follows: combining results from decision-making tasks, such as the IGT with contextual insights gleaned from personality trait assessments and objective data from the physical activity tracker, we can develop a predictive model that can identify those most likely to give up their fitness goals. This information has the potential to be used to create more targeted support to ensure that those who embark on fitness programs are successful. This study also acts as a feasibility model to test the deployment of questionnaires and the IGT using a *bring your own device* (BYOD) model. The intention is to incorporate feedback from compliance and acceptance testing to inform future studies.

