### Recruitment

The study will be advertised on social media, commencing in 2021. This is an entirely virtual, BYOD study design, and interested individuals without any underlying health issues and over the age of 18 years will be invited to download the study app from the Google Play store (Alphabet Inc) and Apple App Store (Apple Inc). Those who are willing to consent to the study and own a Fitbit (Fitbit Inc) will be requested to participate in the study. Once consent is given to participate in the study, participants will be asked to share their Fitbit data. Physical activity, sleep, and heart rate data will be shared using an anonymized token system to ensure that only pseudonymized data are included in the study. Once the individuals provide consent to participate in the study and share their Fitbit data, they will be asked to complete the following assessments: demographics, Type D personality, goal-setting, and self-efficacy questionnaire. They will also be asked to perform decision-making games based on the IGT.

Metrics concerning compliance with each assessment will be quantified. Data will be captured over 12 months. At the end of the study period, participants will be sent a notification to thank them for their participation and a link to where the study results will be shared once available.

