### Data Analysis and Computational Modeling

This study aims to investigate whether we can predict adherence to self-made fitness goals and identify potential behavioral phenotypes based on the changes in the participants’ responses to a series of validated instruments, including self-efficiency, status of change, and Type D personality, and their behavioral performance on the IGT over 6 months. A range of data analysis techniques will be applied to the collected data to achieve this goal.

We term the results obtained from questionnaires and decision-making tasks as predictor variables, whereas the adherence levels of the participants to fitness goals as target variables for convenience of description. The first problem that must be addressed before predicting and clustering is to quantify both the predictor variables and target variables.

Self-efficiency was measured by an instrument including 18 items using the original 0 to 100 numerical rating scale, where 0 represents *cannot do at all* and 100 represents *high certainty to do.* The Type D personality questionnaire also uses numerical rating scales, although with different ranges from 0 representing *false* to 4 representing *true*. However, for the Status of Change questionnaire, the answers were categorical scales of *yes* or *no*. Thus, the one-hot encoding technique, one of the most common encoding methods in machine learning, will convert the categorical answers to numerical formats.

To evaluate participants’ performance on the IGT, both superficial behavioral variables and underlying cognitive parameters will be summarized and estimated from the behavioral data set. Specifically, 2 parameters will be measured in the behavioral summary analysis. The first parameter will be the total amount of gain by the end of the task, and this parameter will be used to measure the overall performance of the IGT. The second parameter will be the IGT learning scores across the task, that is, the difference between the number of good deck selections and that of bad deck selections across the task, used to reflect the learning process in the task. The 100 trial choices will first be divided into five blocks of 20 trials, each without overlap, and the learning score will be calculated for each block. As a result, 5 variables (learning scores) will be created for this measure.

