## Discussion

### Overview

The rationale for this study is to determine whether data from decision-making games and personality traits could predict individuals most likely to give up on self-determined physical activity goals. The ability to identify the digital persona of those most likely to abandon exercise goals has significant value to those involved in developing targeted support to encourage and adhere to fitness goals.

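### The aim is to predict abandonment of participants' own fitness goals, but the only target variable scores attainment of the WHO weekly minimum

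*Protocol article*

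**What the plan says.** The article describes what it wants to predict in four places:

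- Abstract, Objective: "identify digital personae most likely to be nonadherent to self-determined exercise goals".
- Study Hypothesis: "we can develop a predictive model that can identify those most likely to give up their fitness goals".
- Data Analysis and Computational Modeling, opening: "This study aims to investigate whether we can predict adherence to self-made fitness goals". The same section names "the adherence levels of the participants to fitness goals as target variables".
- Discussion, Overview: "predict individuals most likely to give up on self-determined physical activity goals".

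The end of Data Analysis and Computational Modeling then defines the target in full. It cites the WHO guideline of 150 moderate or 75 vigorous minutes a week. The weekly score is 1 "If the participant completes this minimum exercise in a particular week" and 0 otherwise, and the weekly scores are added to give each participant's adherence level. No other target is defined.

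The WHO figure also appears under Status of Change in the Introduction, where it is chosen as a guideline for the study, and under Status of Change in the Methods, where it gives participants a common standard for answering that questionnaire.

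**The concern.** The stated construct belongs to the individual: did this person keep to, or give up, the goal they set? The target is external and the same for everyone: did this person reach a public-health threshold this week? These are different quantities unless the participant's goal happens to be the threshold.

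The regression algorithms listed under Making Predictions and Clustering need a target, and this is the only one defined. If the plan is followed exactly, a good model would show that questionnaire and Iowa Gambling Task results predict WHO attainment, but it would be reported as predicting who abandons their goals. The hypothesis as worded would not have been tested. Participants can be ranked wrongly in both directions: someone fully adherent to a modest goal can look nonadherent, and someone who has given up an ambitious goal can look fully adherent.

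**Working it through.** The plan has no figure of its own to reproduce on this point. The check has two parts.

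**1. Does the article link the two constructs?** The link would hold if participants adopted the WHO minimum as their goal, or had to hold it as their goal to enter. Neither is stated. Research Participants asks only for self-certified healthy adults over 18 who are starting a physical activity regime and own a Fitbit and a smartphone. The two Status of Change sections use the WHO figure as a guideline and as a questionnaire yardstick, not as a personal goal.

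**2. What does the scoring rule do?** Let m be a participant's moderate minutes in a week and g the participant's own weekly goal in moderate minutes.

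- Plan's weekly score: 1 if m ≥ 150, otherwise 0.
- Own-goal weekly score: 1 if m ≥ g, otherwise 0.
- Each is summed over 52 weeks (data are captured for 12 months).

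The goals and minutes below are illustrative assumptions. Only the 150-minute threshold and the 12 months come from the article.

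| Assumed profile | Plan's score | Own-goal score |
|---|---|---|
| g = 90; m = 100 every week | 100 < 150, so 0 of 52 | 100 ≥ 90, so 52 of 52 |
| g = 300; m = 300 for 8 weeks, then 160 for 44 weeks | 8 + 44 = 52 of 52 | 8 + 0 = 8 of 52 |
| g = 150; m = 160 for 26 weeks, then 0 for 26 weeks | 26 of 52 | 26 of 52 |

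The first two rows reverse the ranking: the person who kept the goal gets the lowest possible score and the person who gave it up gets the highest. The third row has a goal equal to the threshold, and the scores match.

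Two further cases mark the limits of the problem:

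- With g = 90 and m = 160 every week, both scores are 52. A small goal alone does not produce a zero; actual activity must also stay below the threshold.
- A kept goal of 80 vigorous minutes passes the alternative threshold, since 80 ≥ 75, and again both scores are 52.

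So the scores can agree for other goals, depending on what the person does, but agreement is assured only when the goal equals the WHO minimum.

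**The case against.** The strongest defence is that a common yardstick was chosen on purpose. The article adopts the WHO recommendation as its guideline, the threshold is objective, and it makes participants comparable. Personal goals differ in difficulty, so a score against them rewards an easy goal. All of this stands as an argument for keeping the WHO score. It does not make that score a measure of adherence to a self-set goal. A second defence, that this is an observational study which also serves as a feasibility test, bears on urgency and leaves the mismatch in place.

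A reader might also infer several stronger things that the article does not support:

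- **Every kept goal below 150 minutes scores zero.** It does not. The score depends on minutes done, and 75 vigorous minutes also suffice.
- **A stated share of the 200 participants is misclassified.** The article gives no distribution of personal goals, so any count would be invented.
- **Incidental activity counts, so an active job could earn full marks.** The target refers to exercise and relies mainly on activity patterns and step counts, without saying how minutes are filtered. The sentence "Participants were asked to consider only planned physical activities aimed at improving or maintaining physical fitness and health" is an instruction for the stages-of-change questionnaire and does not conflict with a tracker rule.
- **Goal data are collected and then ignored.** Recruitment lists "demographics, Type D personality, goal-setting, and self-efficacy questionnaire", but the Assessments section describes no goal-setting instrument. It does describe the status-of-change questionnaire, which the Recruitment list omits. The goal-setting entry may be that questionnaire, and its answers are used as predictors.
- **WHO attainment was largely settled before enrolment.** Nothing in the text shows this; the study recruits novices who are starting a regime.

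**Conclusion.** The concern holds as a mismatch between the stated aim and the defined target. The Objective, the analysis aim and the Discussion concern self-determined or self-made goals, and the hypothesis concerns participants giving up their own goals. The single target measures attainment of the WHO weekly minimum. Both sides are written out in the same article, so this is not a detail left to a fuller plan.

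For an individual the effect can be as large as the scale allows (0 against 52 in one assumed profile, and 52 against 8 in another). Its frequency among the 200 planned participants cannot be estimated from the article. The conclusion rests on one reading: that the WHO minimum is not itself each participant's goal. If the full protocol makes it so, by instruction or by entry criterion, the mismatch disappears and the article need only say so.

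**What to change.** Record each participant's weekly goal at enrolment, as minutes or sessions together with intensity. Make the primary weekly score 1 if that goal was met on tracker data and 0 otherwise. Keep the WHO-based score as a secondary target.

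If no goal can be recorded, leave the target as it is and restate the objective, hypothesis and conclusions as predicting attainment of the WHO weekly minimum. Scoring against a fraction of a participant's early activity is not a substitute: it measures decline from a baseline and still says nothing about the goal.

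The cost is one structured app item plus changes to the analysis text. Recruitment was still pending at submission, so no data would be lost. The app had been built and ethics approval was in place, so the new item may need a minor ethics amendment. Scores against personal goals are less comparable between participants because goals differ in difficulty, which is the reason to keep the WHO score alongside. Restating the aim costs only wording, but it gives up the question the study set out to answer.

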### Study Interventions

#### Study App

The study app was developed by Dublin City University (AthenaCX, DCU). It allows researchers to rapidly design and deploy mobile experience sampling apps (iOS and Android), including integrated consenting and wearable data collection devices. This will provide the participants with a study overview in the form of plain language statements and privacy statements and facilitate the participants e-consent into the study. The app was designed to ensure that subjects have read the study details and consented to the study before completing the study assessments (Multimedia Appendix 1 includes a text sample from the plain language statement and informed consent in the mobile app). The participants have the right to withdraw from the study at any time. The app will be used to deliver the assessments and provide a link to the decision-making game. Push notifications will be sent to the participants during the study, requesting them to complete the assessments at the required time intervals, as detailed below.

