### Methodological Limitations

#### Recruitment

Participants will not be incentivized to join the study, and as such, it may be challenging to reach the recruitment goals. A rolling strategy will be adopted with regular push notifications to social media and a dedicated study page established on Facebook to maximize recruitment. These pages will have details of the study, the app, and a YouTube instructional video.

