#### Loss of Fitbit Data

All Fitbit devices have a finite internal memory, and intraday data are stored for 5 to 7 days, depending on the tracker (daily totals are generally retained for 30 days). If participants do not regularly synchronize their devices, the data can be overwritten.

Participants may fail to complete the required number of tests in the IGT to facilitate parameter modeling and derive the required insights.

Depending on the number of participants recruited for the study, the application of deep learning approaches may be limited owing to the participant numbers and may result in overfitting.

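### The adherence target is a raw sum of weekly 0/1 scores with no count of observed weeks, so a week without data counts the same as a week without exercise

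*Protocol article*

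**What the plan says.** The rule is in the Protocol article, Data Analysis and Computational Modeling. Adherence is judged mainly from Fitbit activity patterns and step counts. If the WHO weekly minimum is completed, the participant's score is 1: "their adherence score for this week will be 1; otherwise, the score is 0". The weeks are then combined: "The scores for all weeks will be summed to obtain a total score to represent the overall adherence level of this participant". The regression algorithms are applied to the data after cleaning (see Making Predictions and Clustering), and nothing is said there about how weeks lacking data are handled.

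Other sections make it clear that some weeks will lack data:

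- Recruitment (Methods) sets the length of follow-up: "Data will be captured over 12 months".
- Loss of Fitbit Data states that "intraday data are stored for 5 to 7 days, depending on the tracker" and that "daily totals are generally retained for 30 days". It then warns: "If participants do not regularly synchronize their devices, the data can be overwritten".
- Study App states: "The participants have the right to withdraw from the study at any time".

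Data loss is listed as a limitation, but no section connects it to the adherence score.

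**The concern.** The weekly score has two states and the total has no denominator. A participant whose data stop arriving collects zeros from then on, whether or not exercise continued. The score cannot separate someone who stopped exercising from someone who stopped syncing, took the tracker off or left the study.

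This touches the study's main question, which is who will give up a fitness goal. Every supervised model is trained on this total. The predictors (self-efficacy, Type D personality, status of change, Iowa Gambling Task behaviour) could plausibly affect how people engage with an app and a tracker as well as how much they exercise. To the extent that they do, a model could appear to predict abandonment of exercise when it is partly predicting the end of data sharing.

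**Working it through.** **Does the result depend on how the 0 clause is read?** On a strict reading, an unobserved week is scored 0. On a generous reading, it is skipped. In a raw sum both add nothing, so the total is the same. It is too low whenever an unobserved week was in fact adherent, and it can never be too high for this reason.

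**Inputs.** Follow-up is 12 months, taken as 52 weekly scores. The planned sample is 200 (Abstract, Methods). The article gives no weekly adherence rate p, no share of unobserved weeks m, and no link between data loss and the predictors. These three are assumptions below. The plan states no figure of its own to reproduce.

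**Expected total** = 52 × p × (1 − m)

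| p | m = 0 | m = 10% | m = 25% | m = 50% |
|---|---|---|---|---|
| 0.3 | 15.6 | 14.0 | 11.7 | 7.8 |
| 0.5 | 26.0 | 23.4 | 19.5 | 13.0 |
| 0.7 | 36.4 | 32.8 | 27.3 | 18.2 |

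**Two participants with the same score.**

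- Adherent in 60% of weeks, withdraws at week 26: 26 × 0.6 = 15.6. Had exercise continued at that rate under observation, the total would be 52 × 0.6 = 31.2.
- Adherent in 30% of weeks, fully observed: 52 × 0.3 = 15.6.

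**Effect on associations (simulation).** There were 4,000 runs of 200 participants, with p drawn from Beta(2,2) independently of a standard normal predictor x, and logit(m) = −1.1 + b·x. Because x has no relation to exercise, any association with x is spurious. Significance was judged at the two-sided 5% level.

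| b | mean m | mean r, x with raw sum | significant | mean r, x with adherent/observed | significant | r, raw sum with true p |
|---|---|---|---|---|---|---|
| 0 | 25% | 0.00 | 4.8% | 0.00 | 5.0% | 0.94 |
| 0.5 | 26% | −0.25 | 95% | 0.00 | 5.3% | 0.90 |
| 1.0 | 29% | −0.44 | 100% | 0.00 | 5.6% | 0.81 |

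With no link between data loss and the predictor (b = 0), no spurious association appears. Smaller losses do less harm. In a separate run with a lower true mean (about 17 of 52 weeks) and b = 0.5, about 11% loss gave r of about −0.08 and about 5% loss gave about −0.04.

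**A check on the obvious repair.** The proportion column looks clean because, in this simulation, weeks go missing at random given the participant. Take someone who exercises for 10 weeks, then quits and removes the tracker. The raw sum gives 10 of 52 (19%). The proportion of observed weeks gives 10 of 10 (100%) and hides the abandonment.

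**The case against.** The strongest reply is that the 0 clause simply contrasts meeting the minimum with not meeting it, that a cleaning step is planned, and that an article may leave wear-time and withdrawal rules to a fuller document. That would answer a complaint about missing detail. It does not answer this point: the article fixes a raw sum, and a raw sum treats a skipped week and a zero week alike. It is true that the article does not say whether a withdrawn participant's total enters the models, so the withdrawal example applies if it does.

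Second, daily totals last about 30 days. If weekly active minutes can be rebuilt from them, a short sync gap need not lose the week. This stands: it narrows the problem to longer gaps, non-wear and withdrawal.

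Third, the size rests on assumptions. This also stands. A reader might infer from the simulation that the planned models will produce false predictors. The documents do not support that, since they give neither a missing-data rate nor evidence that data loss follows the traits.

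Fourth, scoring missing weeks as 0 can be defended as conservative in a study of people who give up, because some unworn weeks are true nonadherence. This stands in part: it is a reason to keep that score in view, but not as the only target.

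A reader might also infer that late joiners have fewer weeks, since "A rolling strategy will be adopted with regular push notifications to social media" and results are expected in 2022. The documents do not support this. The rolling strategy concerns advertising, the publication year is a forecast, and no common data cut is stated.

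**Conclusion.** The point holds. As written, the target cannot distinguish weeks without exercise from weeks without data, and it errs only downward. The equal totals of 15.6 follow from the scoring rule and the chosen rates of 60% and 30%.

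The consequence depends on why data are lost. If loss is related to the predictors, their associations with the target are biased. If it is not, the total is noisier and lower but no false predictor arises. The size in this study cannot be derived from the article; the table and simulation are illustrations under assumed rates. Nor should the proportion of observed weeks be taken as simply correct, because it can turn an early quitter into a perfect adherer.

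**What to change.** 1. Define in advance what makes a week observed (valid wear), using the activity and heart-rate data already being collected. Use retained daily totals to recover short sync gaps where that is possible.
2. Set unobserved weeks to missing instead of letting them add 0.
3. Replace the raw sum with adherent weeks out of observed weeks, for example in a binomial model with observed weeks as the denominator.
4. Report the missing-as-0 score beside it. It is the lower bound on adherent weeks. The proportion instead assumes that unobserved weeks resembled the observed ones; this is the optimistic side if quitters also stop sharing data, though not a strict upper limit.
5. Analyse the number of observed weeks, or time to the last synced week, as a separate outcome, so that stopping exercise and stopping data sharing can be told apart. A predictor related to the missing-as-0 score and to data sharing, but not to the proportion, should not be presented as a predictor of giving up exercise.

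The cost is a few added rules in the analysis plan and some programming; no new data are needed. The drawbacks are that a wear cut-off has to be chosen and that participants with few observed weeks are estimated imprecisely.
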